#### Tertiary outcomes

The following tertiary outcomes are only addressed in a sub-sample of participants consenting to genetic analyses:Relationship between factor XIII deficiency (i.e., activity after cryopreservation <70%) and risk of cSDH recurrencePredisposition of genetic variants F13A1 rs2815822 and F13B rs12134960 for factor XIII deficiency

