### Sample size {14}

Because of the potential of notable morbidity, recurrent cSDH is considered both a clinically relevant and methodologically reliable, objective primary trial endpoint.

In one of the largest studies to date, Ban et al. compared a prospective series of 72 patients with cSDH undergoing MMA embolization with a historic standard-of-care group of 469 subjects. The overall risk difference (irrespective of hematoma evacuation) was estimated at 26% (95% CI 21 to 31%) in favor of endovascular management. There is much variability in reported cSDH recurrence risks with either treatment option, and unclarity about the realistic benefit of combined surgical and interventional therapy.

In view of the results of published studies (in particular Ban et al.), we conservatively presume recurrence rates of 30% in the control and 10% in the experimental arm during an observation period of 3 months.

Since our assumptions are subject to uncertainty, we will employ an adaptive design according to O’Brien-Fleming with one planned interim analysis to decide about the further trial progress, and to modify the target sample size if necessary and/or reasonable. For a power of 80% and a total alpha of 5%, data from 138 patients (i.e., 69 per group) are needed to detect a risk difference of 20% by a *z*-test for independent samples. Assuming a drop-out and lost-to-follow-up rate of 10%, we plan to enroll 154 patients (i.e., 77 per treatment arm) unless the interim look prompts any adjustment.

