### Plans for collection, laboratory evaluation, and storage of biological specimens for genetic or molecular analysis in this trial/future use {33}

Blood drawn from patients at baseline will routinely be analyzed for platelet count, activated partial thromboplastin time (aPTT), and fibrinogen concentration. For study purposes, we will analyze factor XIII concentration by means of STA-R (Stago, Düsseldorf, Germany) with HEXAMATE Factor XIII (Roche Diagnostics, Basel, Switzerland), and the presence of genetic variants F13A1 rs2815822, F13B rs12134960, F13A1 rs2815822 (C > A) and F13B rs12134960 (C > G). To determine factor XIII activity, blood samples will be cryopreserved for later analysis.

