## Statistical methods

### Statistical methods for primary and secondary outcomes {20a}

The primary outcome, i.e., reduction in cSDH recurrence through the experimental, surgical plus endovascular treatment, compared to surgery alone, will be analyzed using a chi-square fourfold test for independent samples. The two-sided significance level *α* is set at 5% and the power at 80%. Superiority of the experimental intervention over control is assumed, if the resulting *p*-value is below the nominal significance level of 0.00031 at the time of interim analysis (prompting early trial termination), or the nominal significance level of 0.0469 at the time of final analysis.

Secondary categorical outcomes will be investigated by the Cochran-Mantel-Haenszel (CMH), chi-square, or Fisher’s exact test (if one of the cell frequencies is <5). Recurrence-associated complications, complications associated with endovascular embolization, and (serious) adverse events will be expressed as absolute and relative frequencies.

Exploratory analyses will be performed for the distribution of genetic variants and their correlation (by Pearson’s *phi*-coefficient) with factor XIII deficiency (<70%) across the entire cohort without stratification for the type of intervention. The closer the *phi*-coefficient to 1 or -1, the stronger the association (or predisposition) between genetic variants and factor XIII deficiency. Advanced analyses will be performed to study the association between heterozygous, homozygous, and wild type variants, factor XIII activity, and cSDH recurrence.

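### The rule for reading phi as strength of genetic predisposition ignores its dependence on the margins, and phi addresses factor XIII deficiency although the stated objective is activity (minor, exploratory)

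*Protocol article*

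**What the plan says.** The Tertiary objectives under Objectives {7} ask how the F13A1 and F13B variants relate to factor XIII activity. The Tertiary outcomes under Outcomes {12} recast this as predisposition for deficiency, with deficiency defined as "activity after cryopreservation <70" percent, and add that these outcomes are "only addressed in a sub-sample of participants consenting to genetic analyses".

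The section on biological specimens {33} records "the presence of genetic variants F13A1 rs2815822, F13B rs12134960" and has samples frozen so that activity can be determined later. A measured activity will therefore exist for each participant in the sub-study.

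The statistical methods section {20a} labels the genetic work exploratory. It correlates the variants by phi "with factor XIII deficiency (<70%) across the entire cohort without stratification for the type of intervention". Its reading rule is that the nearer phi is to 1 or -1, "the stronger the association (or predisposition) between genetic variants and factor XIII deficiency". The next sentence reads: "Advanced analyses will be performed to study the association between heterozygous, homozygous, and wild type variants, factor XIII activity, and cSDH recurrence". No model or effect measure is attached to that sentence.

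**The concern.** A signed phi describes a 2x2 table, here carrier or non-carrier against deficient or not. Its largest and smallest possible values are fixed by the two margins. A rule that equates distance to ±1 with strength of predisposition treats ±1 as reachable, which in general it is not. Two consequences follow. A rare variant that fully predisposes its carriers can be reported as a modest association. And the phi values of the two named variants, whose carrier frequencies need not agree, invite a comparison that they cannot support.

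There is also a mismatch of scale. The objective is about activity, yet the only method named in the article discards the measured value in favour of a cut at 70%. What is at stake is the interpretation of a tertiary finding, not the treatment comparison.

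**Working it through.** **Inputs.** From the protocol: the 70% cut, the phi-coefficient, its reading rule, and pooling over both arms. Not given: carrier frequency p, deficiency prevalence q, and the size of the consenting sub-sample. Values of p and q below are assumptions, shown as a range. The protocol states no expected phi or prevalence, so there is no figure to reproduce.

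**1. Bounds of phi.** With a = min(p, q) and b = max(p, q):

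phi_max = √[a(1−b) / (b(1−a))], and phi_min(p, q) = −phi_max(p, 1−q).

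So +1 needs p = q, −1 needs p = 1−q, and both together need p = q = 50%.

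**2. A fully predisposing variant.** If carriers are no more common than deficient patients (p ≤ q), the maximum is reached when every carrier is deficient. For p = 5%, q = 30%:

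phi_max = √[0.05 × 0.70 / (0.30 × 0.95)] = √0.1228 = 0.35, with phi_min = −0.15.

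In that table 100% of carriers are deficient, against (0.30 − 0.05)/0.95 = 26.3% of non-carriers, a risk difference of 73.7 percentage points. Other cases in which every carrier is deficient:

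| Carriers p | Deficient q | phi |
|---|---|---|
| 5% | 5% | 1.00 |
| 5% | 10% | 0.69 |
| 5% | 20% | 0.46 |
| 10% | 20% | 0.67 |
| 10% | 30% | 0.51 |
| 20% | 30% | 0.76 |
| 5% | 50% | 0.23 |

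The same complete predisposition gives anything from 0.23 to 1.00 in this table.

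**3. Comparing two variants.** Take a second variant with p = 30%, q = 30% and phi = 0.35. The joint frequency is 0.30 × 0.30 + 0.35 × √(0.30 × 0.70 × 0.30 × 0.70) = 0.09 + 0.0735 = 0.1635. The risk of deficiency is 0.1635/0.30 = 54.5% in carriers and (0.30 − 0.1635)/0.70 = 19.5% in non-carriers, a difference of 35 points. Both variants have phi 0.35, but the risk differences are 73.7 and 35 points.

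**4. Information lost by the cut.** For a small shift in a normal variable cut at quantile z_q, the asymptotic efficiency relative to the uncut value is f(z_q)² / [q(1−q)], where f is the standard normal density.

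| Deficient q | Efficiency | Loss |
|---|---|---|
| 5% | 0.224 | 78% |
| 10% | 0.342 | 66% |
| 20% | 0.490 | 51% |
| 30% | 0.576 | 42% |
| 50% | 0.637 | 36% |

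This is the loss from cutting activity alone. Merging heterozygous and homozygous carriers is a separate simplification and is not counted here.

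**The case against.** The best defence is that phi fits the outcome to which it is attached. The tertiary outcome is deficiency, which is binary by definition, and the specimen section speaks of the presence of a variant, so a carrier-by-deficiency table is natural. For fixed margins a phi further from zero does mean a stronger association. All of this stands: phi is a legitimate 2x2 description, and what fails is its use as an absolute scale and across variants.

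Four stronger readings are tempting, and the documents do not support them.

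- A reader might infer that phi is the only analysis planned, so that three genotypes and measured activity are ignored. The sentence after the rule plans both. That it names no model is no finding in itself, because an article commonly leaves this to the full protocol or analysis plan.
- A reader might say that the cut wastes half the information. That holds only if roughly 15% to 25% of patients are deficient, a figure that the protocol does not give.
- A reader might conclude that a real genotype effect would be missed. Simulated power can illustrate this. With 138 patients, allele frequency 0.2 and 0.35 SD per allele, power is about 63% for continuous activity, against 29% to 40% for phi with cuts at the 10th to 50th percentile. But the effect, the allele frequency and the additive model are assumed, 138 is the evaluable total in Sample size {14} and not the sub-sample, and the protocol announces no significance test of phi.
- A reader might take a low ceiling with carriers more common than deficient patients as proof of the problem. With 40% carriers and 10% deficient the ceiling is 0.41, but at that ceiling 75% of carriers are not deficient, so the variant is not fully predisposing. The case needs carriers rarer than deficiency.

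**Conclusion.** The reading rule is badly fixed. A fully predisposing variant can give a phi of 0.35 (5% carriers, 30% deficient), and phi values for two variants with different frequencies cannot be ranked. The only method named in the article also addresses deficiency where the objective is activity, at a loss of about 36% to 78% of the information for 50% down to 5% deficient. The bounds of phi are exact; the frequencies put into them are assumed. The loss assumes normality and is asymptotic. The further analyses in the same section reduce the scale mismatch, since they bring in activity and all three genotypes, but they do not correct the rule.

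The severity is minor. The work is exploratory and tertiary, rests on a consenting sub-sample, and has no bearing on the primary conclusion.

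**What to change.** In the statistical methods section {20a}:

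1. Delete the sentence that reads strength from the distance of phi to ±1, or qualify it by saying that the range depends on carrier and deficiency frequencies and that values are not comparable between variants.
2. Report the carrier-by-deficiency table (cut at 70%) for each variant with an odds ratio or risk difference and 95% CI. If every carrier is deficient, a cell is empty and the odds ratio estimate is infinite, so the risk difference is then the more useful figure.
3. For the objective on activity, name as the main analysis a regression of continuous factor XIII activity on allele count (0, 1, 2), one variant at a time, giving the difference in percentage points per allele with its 95% CI.

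The cost is a change of wording, repeated in the full protocol or analysis plan if the same rule appears there. The samples, assay and patients stay the same.

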### Interim analyses {21b}

The planned interim analysis according to the O’Brien-Fleming design will be conducted after the recruitment of half of the target sample. Given the predicted recruitment speed and rate will be reached on time, the interim analysis will be conducted 12 months after first-patient-in (plus 3 months of follow-up), corresponding to 77 included patients and 69 evaluable data sets. If a statistically significant advantage in the recurrence rate of the experimental group can be demonstrated at the time of the interim analysis with a *p*-value of the chi-squared test of <0.0031, the experimental therapy will be assumed to be superior to the standard of care, leading to premature termination of the study. If the effect size is lower than presumed, a larger sample size and enrolment of additional trial sites must be considered. Investigators will discuss this option together with the funding body and the DSMB. If the likely risk difference between treatments is much smaller than expected and the recalculated sample size exceeds numbers which cannot be achieved, the trial will be terminated for futility. The trial will also be terminated early if the surgery-only control group turns out to be superior to combined management in any case, or if major novel scientific evidence shows any substantial favor of one over the other approach.

### Methods for additional analyses (e.g., subgroup analyses) {20b}

Primary and secondary outcomes will be stratified for age in a categorial manner (i.e., ≤67 and >67 years, the common retirement age in Germany).

### Methods in analysis to handle protocol non-adherence and any statistical methods to handle missing data {20c}

The primary analysis will be performed on the modified intent-to-treat (mITT) set including all randomized patients and based on the treatment arm they were randomized to, regardless of the therapy they actually received. The modification of the ITT set implies that study outcomes must be fully documented at the follow-up visit at 3 months. The per-protocol (PP) set is used for sensitivity analyses, including participants who were treated in full accordance with the study protocol and actually received the randomly assigned treatment.

A missing data analysis will be conducted investigating the extent and type of missing values in trial endpoint variables. In case of a suspected non-random missing data mechanism (e.g., Missing At Random [MAR], Missing Not At Random [MNAR]), corresponding sensitivity analyses will be carried out along with a discussion of the results. If suitable, we will consider multiple imputation (MI) to fill empty cells in the dataset.

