### Criteria for discontinuing or modifying allocated interventions {11b}

Patients may withdraw their consent at any time without providing a reason and thus terminate their participation in the study prematurely. Withdrawal from the study and reasons, if known, will be documented. Criteria for premature drop-out include:Subsequent occurrence of an exclusion criterionLoss of contactDeathDeclaration of withdrawn consent

Moreover, the principal investigator is entitled to terminate the study prematurely if:Patient recruitment remains inadequate despite multiple measures to improve enrolmentSerious problems with the quality of collected data cannot be resolvedUnforeseeable circumstances at the trial center prevent trial continuationUnacceptable risks arise (after a risk-benefit assessment by the Data Safety Monitoring Board)New scientific findings in favor of one or the treatment violate the equipoise principle

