### Outcomes {12}

#### Primary outcome

The primary outcome is cSDH recurrence up to 3 months after surgery. Recurrence is defined by one and/or both of the following criteria:Recurrent cSDH with at least the same volume (±10%) compared to baseline findingsRecurrent cSDH which requires surgery

Recurrence of cSDH is operationalized as a binary outcome (i.e., recurrence or no recurrence) during a follow-up period of 3 months.

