### Participant timeline {13}

Participants in the intervention and control groups will undergo five and four scheduled follow-up visits, respectively (Table 1):*−t*_1_ Screening and informed consent*t*_0_ Randomization*t*_1_ Baseline*t*_2_ Embolization (intervention group only, within 72 h after surgery)*t*_3_ Follow-up 1 month after baseline (± 1 week)*t*_4_ Follow-up 3 months after baseline (± 1 week)

**Table 1 Tab1:** Schedule of enrollment, interventions, and assessments

	Study period					
	Enrollment	Allocation	Post-Allocation			Close-Out
Time point	*−t*_*1*_	*t*_*0*_	*t*_*1*_	*t*_*2*_	*t*_*3*_	*t*_*4*_

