### Plans to promote participant retention and complete follow-up {18b}

Neurosurgical hematoma evacuation and endovascular MMA closure represent standard modalities both at the trial site and in the scientific community- the novelty of MEMBRANE is random assignment to surgery plus endovascular treatment versus surgery alone. Patients will deliberately be informed that trial participation guarantees no personal benefit whatsoever- however, it will also be explained there is scientific evidence that patients treated in a clinical trial environment may show superior outcomes compared to those managed under routine practice conditions.

Investigators, study nurses and other staff will take care of retaining participants until the scheduled last follow-up visits.

Patients who chose to discontinue participation, those who do not respond to multiple attempts of contact or cannot be reached by phone or mail will be considered losses to follow-up. Data will be recorded, stored, and used for final analysis unless participants actively demand data deletion. Those appeals will be handled by local data security officers in accordance with EU-GDPR.

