### Adverse event reporting and harms {22}

All SAEs reported by study participants or observed by an investigator within the study period must be documented in the eCRF. SAEs are any undesirable sign, symptom, or medical condition whichIs fatalIs acutely life-threateningRequires or prolongs inpatient hospitalizationResults in persistent or significant disability/incapacityConstitutes a congenital anomaly or birth defect (not applicable, pregnancy excludes from study participation)

The principal investigator will be informed immediately about the onset of a SAE and must decide whether the participant shall be excluded from or remain in the study. The likelihood of a causal relationship between the individual trial intervention and SAE will be investigated further, and patients will be observed until the SAE resolves or a stable condition is reached.

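### The primary mITT set requires full documentation at the 3-month visit, so a recurrence already documented before then can be dropped from the primary analysis

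*Protocol article*

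**What the plan says.** All references are to the protocol article.

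- **Endpoint (Outcomes {12}, Primary outcome).** "The primary outcome is cSDH recurrence up to 3 months after surgery". It is binary. It is met by a recurrent haematoma of at least about the baseline volume, by a recurrence that needs surgery, or by both.
- **Visits (Participant timeline {13}, Table 1).** CT is scheduled at baseline, 1 month and 3 months; the earlier follow-up visit is listed as "Follow-up 1 month after baseline (± 1 week)".
- **Primary set ({20c}).** "The primary analysis will be performed on the modified intent-to-treat (mITT) set including all randomized patients", analysed by allocated arm. The next sentence narrows this: "The modification of the ITT set implies that study outcomes must be fully documented at the follow-up visit at 3 months". The per-protocol set is used for sensitivity analyses.
- **Drop-out ({11b}).** "Criteria for premature drop-out include:Subsequent occurrence of an exclusion criterionLoss of contactDeathDeclaration of withdrawn consent".
- **After a serious adverse event ({22}).** The principal investigator "must decide whether the participant shall be excluded from or remain in the study".
- **Losses to follow-up ({18b}).** "Data will be recorded, stored, and used for final analysis unless participants actively demand data deletion".
- **Missing data ({20c}).** The extent and type of missing endpoint data will be examined, and sensitivity analyses follow if a non-random mechanism is suspected. On imputation: "If suitable, we will consider multiple imputation (MI) to fill empty cells in the dataset".

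**The concern.** A cumulative endpoint is known as soon as the event happens. Only a patient without an event needs the 3-month assessment to be classified. Section {20c} instead ties membership of the primary set to documentation at that one visit, whether or not the endpoint is already settled. Nothing in the article says that a recurrence seen before drop-out still counts.

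The patients concerned are those who recur and then have no documented month-3 visit. Routes to that state are death, withdrawal, loss of contact and exclusion after a serious adverse event. The last is notable because a recurrence that needs surgery could meet the seriousness criterion of required or prolonged hospitalisation, so the endpoint event can itself open the way to removal. The clinicians who perform the treatments are not blinded ({17a}).

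At stake is a set that is described as including all randomised patients but works as a completer set, with membership that may depend on the outcome. The one sensitivity set that is promised without condition, per-protocol, restricts further and cannot bring the lost events back.

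**Working it through.** **Inputs from the article.** Recurrence 30% in control and 10% in experimental; 69 evaluable and 77 enrolled per arm; 10% drop-out ({14}). Chi-square test at a final two-sided level of 0.0469 ({20a}).

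**The plan's own figures.** 138/0.90 = 153.3, rounded up to 154; 69/0.90 = 76.7, rounded up to 77. The inflation reproduces. With 69 per arm after purely random loss, exact power of the chi-square test at 0.0469 is about 85%. Random loss therefore costs precision only.

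**Assumptions.** The article does not say how many recurrent patients will lack month 3. Let p be the true recurrence rate, l_r the share of recurrent patients lost and l_n the share of others lost, the same in both arms. Then

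observed rate = p(1 − l_r) / [p(1 − l_r) + (1 − p)(1 − l_n)].

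**Case A: l_r = 30%, l_n = 5%**
- Control: 0.30 × 0.70 = 0.210; 0.70 × 0.95 = 0.665; 0.210/0.875 = 24.0%; 77 × 0.875 ≈ 67 patients.
- Experimental: 0.10 × 0.70 = 0.070; 0.90 × 0.95 = 0.855; 0.070/0.925 = 7.6%; 77 × 0.925 ≈ 71 patients.
- Overall loss: 1 − (0.875 + 0.925)/2 = 10%, as planned.
- Risk difference 16.4 points; exact power 77%.

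**Case B: l_r = 20%, l_n = 7%**
- Control: 0.240/(0.240 + 0.651) = 26.9%.
- Experimental: 0.080/(0.080 + 0.837) = 8.7%.
- Risk difference 18.2 points; exact power 82%.

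**Odds ratio.** True: (0.30/0.70)/(0.10/0.90) = 3.86. Case A: (0.210/0.665)/(0.070/0.855) = 3.86. Case B: (0.240/0.651)/(0.080/0.837) = 3.86. The factor (1 − l_r)/(1 − l_n) cancels between arms. With equal true rates of 30% or 20% and Case A loss, exact rejection is 4.6% or 4.9% at the nominal 4.69%, so the test essentially keeps its level.

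**Counting the recurrences in Case A**, if all of them had been seen before loss:
- Control: 0.30/(0.30 + 0.665) = 31.1%.
- Experimental: 0.10/(0.10 + 0.855) = 10.5%.
- Difference 20.6 points; power 88%. The result overshoots 20 because lost non-events are still left out. This is why the fix needs imputation as well.

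**Loss that differs by arm.** Take 8 losses per arm (0.10 × 77 = 7.7), leaving 69.

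| True counts (control vs experimental) | Recurrences among the 8 losses | Analysed | Difference | p |
|---|---|---|---|---|
| 23/77 vs 8/77 | before any loss | 23/77 vs 8/77 | 19.5 points | 0.0026 |
| 23/77 vs 8/77 | 4 control, 0 experimental | 19/69 vs 8/69 | 15.9 points | 0.018 |
| 23/77 vs 8/77 | 6 control, 0 experimental | 17/69 vs 8/69 | 13.0 points | 0.047 |
| 23/77 vs 8/77 | 7 control, 0 experimental | 16/69 vs 8/69 | 11.6 points | 0.072 |
| 15/77 vs 15/77 | 0 control, 4 experimental | 15/69 vs 11/69 | 5.8 points | 0.38 |
| 15/77 vs 15/77 | 0 control, 8 experimental | 15/69 vs 7/69 | 11.6 points | 0.063 |

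The upper rows hide a true benefit and the last two create an apparent one. These are illustrations at the edge, not forecasts.

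**The case against.** The strongest reply is that the affected group may be small. A patient re-operated at week 3 who attends month 3 stays in and counts. If loss depends on recurrence alone, the odds ratio and the level of the test hold, and in the milder case power stays above the planned 80%. Section {20c} also promises a missing-data analysis and, where a non-random mechanism is suspected, sensitivity analyses. All of this stands. It limits the severity, but it does not change the set on which the primary test is run.

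It can also be said that the wording in {20c} may mean only that the outcome under analysis must be known. That reading is possible and would remove most of the problem, but the sentence names the 3-month visit and outcomes in general, so the text needs to say so. Nor is this a detail left to an analysis plan: the article itself fixes the set.

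Three stronger readings are tempting and are not supported:

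- **That the primary result will be biased.** Bias needs loss related to outcome. A spurious benefit needs loss that differs by arm. The documents give no figure for either.
- **That mRS 6 can never be counted.** Section {20c} assigns the mITT set to the primary analysis only. Death is an explicit mRS level in {12}, and fatal events must be documented under {22}. Listing death as drop-out in {11b} does not forbid scoring it; the article simply does not say how it is scored.
- **That {18b} contradicts {20c}.** Section {18b} does not say which analysis uses the data of losses to follow-up, so the two need reconciling but do not clash outright.

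**Conclusion.** The point holds as a badly fixed rule. The primary set is conditioned on a visit, while the endpoint can be settled before it. As written, a documented recurrence leaves the primary analysis when month 3 is not documented.

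The size cannot be derived from the documents. Under assumed loss that is related to recurrence and equal in both arms, the risk difference falls from 20 to between 16.4 and 18.2 points and exact power is 77% to 82%, against about 85% with random loss; the odds ratio stays at 3.86. Loss that differs by arm could bias the comparison in either direction. If loss is unrelated to outcome, only precision suffers. Should-fix.

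**What to change.** 1. Define the primary set as all randomised patients, analysed as allocated.
2. Count any recurrence documented up to 3 months as an event, whether or not the 3-month visit took place.
3. Treat as missing only patients without a documented recurrence whose 3-month status is unknown, and use multiple imputation for them, so that lost non-events are not simply omitted.
4. Keep the set with complete 3-month documentation as a sensitivity analysis.
5. State that death is scored as mRS 6, and how death without recurrence enters the primary endpoint.
6. Reconcile {11b}, {18b}, {20c} and {22}, so that it is clear which data of patients who drop out or are excluded after a serious adverse event enter which analysis.

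The cost is protocol and analysis-plan wording plus a little analysis work. No new visit or measurement is needed. It should be settled before outcomes are compared by arm, including at the interim analysis, which {21b} plans on 69 evaluable data sets from 77 included patients.

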## Interventions

### Explanation for the choice of comparators {6b}

Patients assigned to the control group will be managed according to the current standard of care, i.e., neurosurgical evacuation of cSDH by burr hole trepanation and/or any surgical technique without specific added treatment.

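### The per-protocol set requires embolization, given up to 72 h after the outcome clock starts and in one arm only, so it can drop early recurrences from the intervention arm alone

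*Protocol article*

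**What the plan says.** Four statements in the protocol article matter together.

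- **Outcome clock** (Primary outcome): "The primary outcome is cSDH recurrence up to 3 months after surgery". Either of two criteria is enough: a recurrent hematoma of about the baseline volume, or a recurrence that needs surgery.
- **Timing of embolization** (Participant timeline {13}): "Embolization (intervention group only, within 72 h after surgery".
- **Control treatment** (Explanation for the choice of comparators {6b}): "Patients assigned to the control group will be managed according to the current standard of care", that is, evacuation with nothing specific added. The assigned treatment is complete once surgery is done.
- **Analysis sets** (section {20c}): the primary modified intent-to-treat analysis follows the randomized arm, "regardless of the therapy they actually received", on condition that "study outcomes must be fully documented at the follow-up visit at 3 months". "The per-protocol (PP) set is used for sensitivity analyses", and that set is described as "including participants who were treated in full accordance with the study protocol and actually received the randomly assigned treatment".

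Section {20c} gives the per-protocol set no common start time or landmark. It names no other analysis population for non-adherence.

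**The concern.** Membership of the per-protocol set depends on something that happens after randomization, that only intervention patients have to reach, and that comes after primary events can already count. A control qualifies at surgery. An intervention patient qualifies only at embolization, up to 72 h later. If a recurrence needing surgery in between means that embolization is not done, patient and event disappear from the intervention arm, while the matching control event remains.

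The per-protocol analysis is there to show whether the primary result is robust to non-adherence. A set with a built-in route towards the hypothesis serves that purpose poorly. If the primary result is borderline, a somewhat larger per-protocol effect could be taken as the effect of actually being embolized when part of it is selection.

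**Working it through.** The plan states no figure for early recurrence or for missed embolization, so there is nothing of its own to reproduce. The check shows how large the one-sided removal could be.

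**Inputs from the protocol article**
- Recurrence rates (Sample size {14}): "we conservatively presume recurrence rates of 30% in the control and 10% in the experimental arm". For no treatment effect, 30% is used in both arms.
- 69 evaluable patients per arm (Sample size {14}).
- Two-sided nominal level of 0.0469 at the final analysis (section {20a}), so 2.35% in each direction.

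**Assumptions, not in the documents**
- f: share of 3-month recurrences that fall before embolization. A constant hazard over 90 days, with embolization at the end of the window, gives 3/90 = 3.3%. Values of 10% and 20% represent clustering soon after surgery.
- q: share of those early failures who are then not embolized: 25%, 50% or 100%.

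**Formula.** Before embolization the arms do not differ in treatment, so early recurrences occur at the control rate in both. The fraction of the intervention arm removed, each with an event, is e = 0.30 × f × q. The per-protocol intervention rate is (p − e)/(1 − e), where p is the true 3-month rate in that arm. The control rate stays at 30%.

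**No treatment effect (p = 0.30), q = 100%**
- f = 3.3%: e = 0.01; 0.29/0.99 = 29.3%; spurious benefit 0.7 points; 69 × 0.01 = 0.7 patients removed.
- f = 10%: e = 0.03; 0.27/0.97 = 27.8%; 2.2 points; 2.1 patients.
- f = 20%: e = 0.06; 0.24/0.94 = 25.5%; 4.5 points; 4.1 patients.

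**Spurious benefit (percentage points) when fewer early failures miss embolization, no treatment effect**

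| f | q = 25% | q = 50% | q = 100% |
|---|---|---|---|
| 3.3% | 0.2 | 0.4 | 0.7 |
| 10% | 0.5 | 1.1 | 2.2 |
| 20% | 1.1 | 2.2 | 4.5 |

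**Planned effect (p = 0.10, true difference 20 points), q = 100%**
- f = 3.3%: 0.09/0.99 = 9.1%, difference 20.9 points.
- f = 10%: 0.07/0.97 = 7.2%, difference 22.8 points.
- f = 20%: 0.04/0.94 = 4.3%, difference 25.7 points.

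**Error rate.** By normal approximation with 69 per arm and q = 100%, the chance of a per-protocol result falsely favouring embolization rises from 2.35% to 2.9%, 4.4% and 7.9% for the three values of f.

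**Per patient.** With 21/69 recurrences in each arm, dropping one from the intervention arm gives 20/68 = 29.4% against 30.4%, a shift of 1.0 point. With 7/69 against 21/69, dropping one gives 6/68 = 8.8%, and the difference moves from 20.3 to 21.6 points.

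**Check of the remedy, no effect, f = 10%.** With early failures kept in the set with their events, both arms stay at 30%. With a common 72 h landmark, both arms become 0.27/0.97 = 27.8%. The spurious difference is zero either way.

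**The case against.** The strongest reply is that no trial conclusion rests on this set. The superiority rule in section {20a} and the stopping rules in section {21b} do not refer to it, and the primary analysis follows randomization. That stands: it limits the point to the sensitivity analysis.

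A reader might infer that the set drops everyone who fails before embolization, or that the per-protocol result must look better than the primary one. The documents support neither.

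- The rule removes patients who were not treated as assigned. One who is re-operated and still embolized within 72 h can stay. Nothing in the article says that early failure rules out embolization.
- Death and clinical deterioration are not primary events. Death is a drop-out reason in both arms (section {11b}). An acute or subacute hematoma is an exclusion criterion, and later occurrence of an exclusion criterion is also a drop-out reason in both arms. Scheduled follow-up CT is at 1 and 3 months. In the first 72 h, therefore, mainly a recurrence needing surgery could operate this route.
- Patients not embolized for anatomical or other reasons also leave one arm only, and their prognosis is unknown. Removing low-risk patients would push the other way. Other protocol deviations can remove patients from both arms.
- At a constant hazard the effect is below one point, and 0.2 points if only a quarter of early failures miss embolization.

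It can also be said that per-protocol detail belongs in an analysis plan that is not shown. That holds for finer handling rules, but the inclusion rule and the role of the set are stated here, and the point concerns that stated rule.

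**Conclusion.** The concern holds in limited form. As stated, the per-protocol rule selects on a post-randomization step in one arm after the outcome clock has started. An early recurrence that prevents embolization is lost from the intervention arm only, and this component can only favour embolization.

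Its size cannot be derived from the documents. Across the assumed ranges it runs from 0.2 to 4.5 points under no effect. The upper end needs 20% of recurrences before embolization and none of those patients embolized. It is negligible unless failures cluster in the first 72 h, although with 69 per arm even one or two patients move the estimate by a point or more.

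The net direction of the per-protocol analysis as a whole is not established, and the primary analysis is untouched by this rule. This is an inexpensive improvement to a sensitivity analysis, not a threat to the trial's main conclusion.

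**What to change.** Amend the per-protocol wording in section {20c} in one of two ways:

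1. Keep in the set, with their event, intervention patients who were not embolized because of a recurrence before embolization.
2. Apply the same 72 h landmark to both arms: include only patients alive and free of recurrence and re-operation at 72 h after surgery, and count recurrences from then to 3 months.

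In either case, label the per-protocol result supportive.

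Optionally, add a complier average causal effect: the difference by randomized arm divided by the proportion embolized in the intervention arm less any proportion embolized among controls. State its assumption that assignment affects recurrence only through embolization. If it is computed in the modified intent-to-treat set, it inherits that set's requirement for a documented 3-month outcome.

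The cost is wording plus the dates of surgery, embolization and recurrence. Option 1 also needs the reason for non-embolization. Option 2 estimates the effect after 72 h rather than from surgery. Neither removes selection by anatomy or frailty, so the number of intervention patients not embolized, with reasons, should be reported beside the result.
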